3	% of needy patients who were provided support	Administrative database & interviews with caregivers	Quarterly for the first 2 years of the programme					Change in caregiver burden score before and after intervention	Zarit Burden Interview-12	Baseline (at enrolment) and every 3 months after enrolmentuntil patients’ death	

								No. of ED attendances, in-patient admission and length of stay (LOS)	Administrative databases	1 month (30 days), 3 months (90 days) and 6 months (180 days) prior to death	

								% of patients with good management of symptoms	PCOC – symptoms assessment		
	
4	% of cases discussed in the MDM (multidisciplinary meetings)	Administrative database		Providers’ working experience	Interviews with providers	At least 6 months after program implementation		Development costs, program implementation costs and healthcare utilization costs	Administrative database	6 months prior to death	
		
	Quality of collaborative and communications between providers	Interviews with providers						Average duration in each PCOC stage		1 month (30 days), 3 months (90 days) and 6 months (180 days) prior to death	
	
5	Implementation experience	Interviews with providers	At least 6 months after program implementation					Perceived quality of care	Mortality follow-back survey	≤3 months after death	
	
*6*	Extent of support from management							Sustainability	Clinical Sustainability Assessment Tool (CSAT)	At least 6 months after program implementation	

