#### Data Collection

Context, mechanisms and relationships between context and outcomes, as defined in phase 1, will be tested through interviews with healthcare providers and users. As suggested by Manzano [29], questions to be asked in these interviews aim to ascertained how the program works, for whom, in what circumstances and how implementation has veered from what was initially planned. A purposive sample of 15 healthcare providers/managers and 15 healthcare users (patient and/or carers) per disease condition will be invited to take part in face-to-face or virtual interviews. The eventual sample size will be determined based on thematic saturation of the study. Data saturation is reached when the ability to obtain additional new information has been attained, and when further coding is no longer feasible [30].

In ensuring the quality of data collected, an interview guide will be used and interviewers will routinely reflect on interview experience and discuss data as they are being collected. Based on emerging understanding and identification of key knowledge gaps throughout the process of interviewing, interview questions will be revised accordingly.

Healthcare services utilization, health outcomes, healthcare cost and caregiver burden data will be collected and analyzed over time to evaluate intervention outcomes of ViP. A quasi-experimental design will be adopted by comparing the outcomes of the intervention group against a comparator group for healthcare utilization, outcomes and cost. Due to limited data available, a pre-post comparison will be made for caregiver burden. A quasi-experimental design is selected as it more truly mimics real-world constraints and provide a balance between internal and external validity [31]. Pragmatically, all patients who agree to participate, are accepted into the home-based PC service, utilized the services for at least one month and passed away as of December 2022 will be included as the intervention group. A retrospective comparator group will be identified from available CGH and SACH clinical databases. We plan to restrict the databases to within CGH and SACH for the identification of comparators. This is because patients are planned to be recruited from CGH and SACH in the first 2 years. This is a way of ensuring comparability between intervention and comparator group while keeping the data manageable.

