Data for both intervention and comparator group will be extracted from SingHealth-iHiS Electronic Health Intelligence System (eHints), a common database of patient level data across all SingHealth institutions. Development and implementation cost will be extracted from ViP program database and potentially finance department. For comprehensiveness, we may also merge dataset with data held by the Ministry of Health to obtain nationwide acute hospital utilization (ED visits, hospital admissions, ICU utilizations, length of stay and date of death) using National Registration Identification Card (NRIC) of subjects included in the study.

Primary informal caregivers of ViP patients will be invited to complete a Zarit Burden Interview (ZBI) – 12 items to assess caregiver burden at enrolment and every 3 months after enrolment until patients’ death. The ZBI is a widely used tool for assessing caregiver burden among those who provide care for patients with various illnesses, including those at the end-of-life [34,35]. A higher score on the ZBI represents higher burden. As suggested by Stagg and Larner, a score of “0–20”, “21–40” and “>40” will be considered as little or no, mild/moderate and high caregiver burden respectively [36].

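### The caregiver-burden bands (0–20, 21–40, >40) fit a 12-item Zarit total poorly unless items score up to 5, so band-based reporting may mislead; the change-in-score outcome is not affected

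*Protocol article*

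**What the plan says.** In the protocol article, Methodology, Phase 2, Data Collection, primary informal caregivers are to "complete a Zarit Burden Interview (ZBI) – 12 items to assess caregiver burden at enrolment and every 3 months after enrolment until patients’ death". The direction of scoring is given: "A higher score on the ZBI represents higher burden". The section then adopts three classes, attributed to a cited source: "a score of “0–20”, “21–40” and “>40” will be considered as little or no, mild/moderate and high caregiver burden respectively".

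Table 2 (under Study Design) names the same instrument, "Zarit Burden Interview-12", and gives the outcome indicator for programme theory 3 as "Change in caregiver burden score before and after intervention". Data Collection adds that, because of limited data, "a pre-post comparison will be made for caregiver burden", with no comparator group for this outcome.

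The article does not give the points per item or the maximum total, and does not say on which version of the instrument the cited bands were derived. The Data Analysis section assigns methods by type of variable (chi-square for categorical, generalized linear models for continuous) and names no analysis that uses the burden bands.

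**The concern.** A fixed threshold on a sum score has meaning only relative to the range of that score. Twelve items give a short range. With common item scorings, a cut at 40 lies close to the top of the range or beyond it, and a cut at 20 lies well up the scale. A caregiver with a substantial total could then be described as having little or no burden, and the top class could hold almost nobody.

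Reducing caregiver burden is one of the five programme aims listed in the section on the intervention. The burden comparison has no control group, so descriptions of the level of burden at enrolment and later will carry weight in interpretation. The quantitative findings are also to be set against the interviews under Data Triangulation. If the bands understate burden, the survey could appear to disagree with what caregivers say when the disagreement comes only from the labels. Movement into or out of a nearly empty class could not be seen either.

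**Working it through.** **Inputs**
- Number of items: 12 (Data Collection; Table 2).
- Bands: 0–20, 21–40, >40 (Data Collection).
- Points per item: not stated. Assumption: 0–4, with 0–3 and 0–5 shown as the range.
- The plan gives no maximum score, sample size or expected distribution for this outcome, so there is no figure of its own to reproduce.

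**Step 1. Range and bands.** Maximum = 12 × top item score. The number of possible whole-number totals is the maximum + 1.

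| Item scoring | Maximum | Totals in 0–20 | Totals in 21–40 | Totals >40 | 20 as share of maximum | 41 as share of maximum |
|---|---|---|---|---|---|---|
| 0–3 | 12 × 3 = 36 | 21 | 16 | 0 | 20/36 = 56% | not attainable |
| 0–4 | 12 × 4 = 48 | 21 | 20 | 8 | 20/48 = 42% | 41/48 = 85% |
| 0–5 | 12 × 5 = 60 | 21 | 20 | 20 | 20/60 = 33% | 41/60 = 68% |

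At 0–4, *high* covers 8 of 49 possible totals (16%). Only 0–5 gives three bands of similar width.

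**Step 2. Mean item score at the band edges.** Threshold ÷ 12:
- top of *little or no*: 20/12 = 1.67 per item;
- entry to *mild/moderate*: 21/12 = 1.75 per item;
- entry to *high*: 41/12 = 3.42 per item.

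If items stop at 4, a caregiver must average 3.42 out of 4 over all twelve items to be classed as high. If items stop at 3, no caregiver can be.

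**Step 3. How full would the bands be at 0–4?** The article gives no distribution, so this is an illustration only: a normal curve truncated to 0–48 with continuity correction, and with assumed means *m* and SDs *s* of 8 and 10.

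P(>40) = [Φ((48.5 − m)/s) − Φ((40.5 − m)/s)] ÷ [Φ((48.5 − m)/s) − Φ((−0.5 − m)/s)]

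For m = 25, s = 8: [Φ(2.94) − Φ(1.94)] ÷ [Φ(2.94) − Φ(−3.19)] = 2.5%. P(≤20) is found the same way, with (20.5 − m)/s as the upper limit.

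| Assumed mean | Share >40 (SD 8 to 10) | Share ≤20 (range over SD 8 and 10) |
|---|---|---|
| 15 | 0.1% to 0.5% | 69% to 75% |
| 20 | 0.5% to 1.8% | 51% to 52% |
| 25 | 2.5% to 5.2% | 29% to 33% |
| 30 | 8.5% to 11.9% | 12% to 18% |

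A mean of 20 is already 42% of the maximum, yet about half of caregivers would be reported as having little or no burden and fewer than 2 in 100 as high. Even at a mean of 30 (30/48 = 63% of the maximum), about 9% to 12% reach the top class.

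**Step 4. What depends on the bands.** Table 2's indicator is a change in score. A label attached to a score does not alter the score, so the pre-post estimate is the same with or without the bands. Only categorical summaries and their interpretation change.

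**The case against.** The strongest reply is that the deciding input, points per item, is not in the article, and that the result runs from an empty top band (0–3) to no difficulty at all (0–5). A top class may also be set deliberately near the end of a scale, so a narrow band is not in itself a wrong one. The bands are attributed to a source that cannot be examined here. No stated analysis, eligibility rule or decision uses them. Finally, a condensed article may leave item scoring to the full protocol.

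Much of this stands, and it rules out several stronger readings that a reader might infer:
- *That high burden cannot be reached at all.* This holds only if items score at most 3, which the article does not say. At 0–4, totals of 41–48 are attainable.
- *That caregivers will be misclassified, or that the bands belong to a longer form.* Either claim needs validated 12-item cut-offs or knowledge of where the bands came from. The article supplies neither.
- *That the conclusion on reducing burden rests on the bands.* Table 2 defines that outcome on the score.

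The reply does not dispose of the point. The finding is not that item scoring was left out. The article states a classification rule for a named 12-item form, and under two of the three scorings shown that rule leaves the top class empty or squeezed into the last eight totals.

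**Conclusion.** The concern holds in a limited form. The bands fit a 12-item total poorly unless items score 0–5. Under the assumed 0–4 scoring, *high* requires at least 85% of the maximum and *little or no* extends to 42% of it; under 0–3 the high band is empty. Under either of these, reported burden levels and movement between bands may be misleading, on an outcome that is a stated programme aim. The estimate of change in the burden score is not affected.

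The band arithmetic rests only on the number of items and the assumed item range. The proportions of caregivers in each band rest in addition on assumed means and SDs, and are illustrations, not predictions.

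**What to change.** Delete the three bands, and report and interpret caregiver burden on the continuous 12-item total that Table 2 already uses, stating the points per item and the maximum score. If categories are wanted, replace the bands with cut-offs confirmed against their source as derived for the 12-item form, and settle this before any data are categorised.

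This is a wording change. It needs no new data and leaves the planned pre-post comparison as it is. The only loss is a simple descriptive label.

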## Data Analysis

Interviews will be transcribed verbatim and each transcript will be checked against recordings for accuracy. Interview transcripts and observation notes will be coded using NVivo. Interviews conducted in languages other than English will be translated and transcribed in English. Like phase 1, interview transcripts will be coded and analyzed by 2 evaluators using NVivo as suggested by Gilmore et al [28]. To ensure the rigor of data analysis, regular meetings will be planned among evaluators to discuss the emerging themes identified in the data. In addition, re-analysis of qualitative data will be conducted if discrepancy is identified. An objective third person will be called in if the discrepancy cannot be resolved between the two evaluators.

Quantitative data analysis will be conducted using STATA. First, univariate analysis will be conducted using chi-square for categorical variables and t-test/ANOVA for continuous variables. Then, to estimate the effect of the program on the outcome of interest, multivariable regression analysis (Poisson or Negative Binominal regression) will be used for count data and generalized linear models will be used for continuous data. For dichotomous outcome variables, logistic regression will be used. Subgroup analysis may be conducted by patients’ primary conditions to allow for the detection of differential effects of ViP on various disease groups. To ensure robustness of the analysis, sensitivity analysis will also be performed.

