Furthermore, as participation in the evaluation efforts is voluntary, we also recognize that selection bias may be introduced in this study. To account for selection bias, demographic information including age, gender, ethnicity and role (for healthcare providers) are collected and will be compared between study participants and those who declined to participate. Given the sensitivity around the topic of PC and prospective data collection methods, difficulties in recruitment and follow-up with respondents are also anticipated. In order to maximize recruitment numbers, evaluators will work closely with main care providers to obtain “buy-in”. If necessary, the recruitment period will also be extended to allow more people to participate. To minimize the numbers lost to follow-up, research appointments are scheduled at participants’ time and place of convenience in collaboration with participants’ healthcare provider. Where loss to follow-up inevitable due to death, survival analysis will be conducted to account for the missing data.

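### Caregiver burden is scored repeatedly in the same carers, but no analysis named fits correlated scores, and the survival analysis offered for loss through death does not fit a change score

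*Protocol article*

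**What the plan says.** Data Collection says that carers complete the ZBI-12 "to assess caregiver burden at enrolment and every 3 months after enrolment until patients’ death". The data framework (Table 2, under Study Design) lists the outcome for the third programme theory as "Change in caregiver burden score before and after intervention". Burden has no comparator group: "a pre-post comparison will be made for caregiver burden". Reducing caregiver burden is also the third of the five programme aims in the description of the intervention.

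Data Analysis gives one list of methods for all quantitative outcomes. For continuous variables the first step is "t-test/ANOVA for continuous variables", and then "generalized linear models will be used for continuous data". It adds that "sensitivity analysis will also be performed", without saying what it will contain. Strengths and Limitations says that, where follow-up is lost because of death, "survival analysis will be conducted to account for the missing data".

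**The concern.** Each carer can contribute several correlated scores, and the quantity wanted is a change within a carer. The list in Data Analysis suits a comparison of independent groups, such as ViP against the comparator, but burden has no comparator. Nothing in the list is stated in a form that handles repeated scores from one person.

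The one remedy named for follow-up cut short by death also belongs to another kind of outcome. Survival analysis models time to an event. By itself it gives no mean change in ZBI-12, no unobserved scores and no within-carer error term.

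Two things are at stake. An insensitive analysis could miss a real fall in burden. An apparent fall could also reflect which carers were still being measured. With the methods as worded, a reader could not tell these apart from a true result.

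**Working it through.** **Inputs.** The article gives no sample size, standard deviation, correlation or power for burden, so there is no stated figure to reproduce. Everything below rests on an assumed within-carer correlation ρ, equal variances at the two times, two-sided 5% and the normal approximation.

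**1. Standard error of the pre-post change.** With n carers scored twice and standard deviation σ, the paired variance is 2σ²(1−ρ)/n. The unpaired formula uses 2σ²/n. The ratio of standard errors is R = 1/√(1−ρ).

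**2. True type I error of the unpaired test.** Its statistic has variance 1−ρ instead of 1, so the true level is 2[1 − Φ(1.96 R)].

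**3. Power where a paired test has 80%.** The paired statistic is centred at 1.960 + 0.842 = 2.802. The unpaired test rejects when the paired statistic exceeds 1.960 R, so power is Φ(2.802 − 1.960 R). The reduced variance of the unpaired statistic must be carried through here; treating it as 1 understates the loss for ρ above 0.5.

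| ρ | R | True level at nominal 5% | Power (paired = 80%) |
|---|---|---|---|
| 0.3 | 1.20 | 0.019 | 68% |
| 0.5 | 1.41 | 0.006 | 51% |
| 0.6 | 1.58 | 0.002 | 38% |
| 0.7 | 1.83 | 0.0003 | 22% |

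At ρ = 0.7, for example: R = 1/√0.3 = 1.826; 1.960 × 1.826 = 3.578; 2.802 − 3.578 = −0.777; Φ(−0.777) = 0.22.

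**4. Drop-out.** I simulated no true change and about half the carers retained, with retention falling as burden rises (log-odds 0.5 to 1.0 per unit of burden, on a scale where a single score has SD 1) and ρ from 0.5 to 0.7. Three estimates of the change are compared, in SD of the score: all baseline scores against remaining follow-up scores; the paired change in carers with both scores; and the likelihood estimate using all available scores, as a mixed model gives.

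| Loss depends on | All baseline v remaining | Paired | Mixed model |
|---|---|---|---|
| carer's stable burden level | −0.12 to −0.31 | about 0 | −0.06 to −0.12 |
| observed baseline score | −0.12 to −0.29 | +0.07 to +0.21 | about 0 |

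The first comparison shows a false fall under both patterns. The paired change is unbiased only under the first pattern, and the mixed model only under the second (missing at random). Loss tied to the change itself would bias the paired estimate too. The two estimates therefore complement each other, and neither removes the need to say how death is handled.

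**The case against.** The strongest objection is that the article never says unpaired, independent or pooled. A paired t-test is a t-test, a repeated-measures ANOVA is an ANOVA, and a generalized linear model can be fitted to one change score per carer or with clustered errors. Table 2 defines the outcome as a change, which fits a paired analysis. A journal article may also leave the exact form of a test to a full protocol or analysis plan that is not shown.

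Most of this stands. A reader might infer that the plan treats the scores as independent, that its intervals are therefore wrong, and that drop-out will contaminate the result. The documents do not support that: those consequences hold only if the methods are run in ordinary form.

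A reader might also infer inflated false-positive rates. Pooling 3 scores per carer at ρ = 0.5 as if independent, to compare groups of carers, would give a true level of 17% (design effect 1 + 2 × 0.5 = 2.0). Pooling 4 at ρ = 0.7 would give 27% (design effect 1 + 3 × 0.7 = 3.1). The article states no such pooling, and subgroup analysis by condition is only a possibility. For the one burden contrast actually planned, the error would run the other way.

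What the objection does not answer is the survival analysis. There the article does choose a method for scores lost through death, and that method does not fit a continuous change score. This is a mismatch in the text and not detail left for later.

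**Conclusion.** The concern holds in a conditional form. The article fixes a repeated, within-carer outcome, names no method in a form suited to it, and assigns survival analysis to missing data that survival analysis does not address for this outcome.

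If the named methods were used in independent-observation form, the standard error of the change would be 1.41 to 1.83 times too large and 80% power would fall to 51% to 22%, for ρ of 0.5 to 0.7. That error is conservative. A false change through drop-out is possible, but its size depends wholly on the assumed pattern and on an all-baseline comparison that the article does not state.

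The point deserves action because burden is a stated programme aim and the correction is cheap. It does not undermine the wider evaluation, in which burden is one of many outcomes.

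**What to change.** In Data Analysis, state that ZBI-12 will be analysed with a linear mixed model with a carer random effect and time since enrolment, using all available scores. Add a paired estimate with its confidence interval for enrolment to first follow-up as a simple supplement.

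For this outcome, replace the survival-analysis sentence in Strengths and Limitations with an explicit treatment of scores cut short by death. One option is a while-alive interpretation, with a joint model of score and time to death as a sensitivity analysis.

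The cost is a few sentences and slightly more analysis work in STATA, the software already named. The mixed model relies on scores being missing at random while the patient is alive, and that assumption should be stated. No new data are needed.

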### Data Triangulation

After both quantitative and qualitative data have been analyzed separately, findings will be integrated through a triangulation process at interpretation stage. The triangulation protocol [37] will be adopted to guide data integration by first producing a convergence coding matrix according to the guiding conceptual frameworks to display findings emerging from each component followed by consideration of where there is agreement, partial agreement, silence or dissonance between findings from different data sources. Assessment of the fit of data integration will be conducted by examining the coherence of findings from various methods used, as suggested by Fetters et al. [38]. Data on contexts, mechanisms and outcomes will then be linked according to the RE CMO configuration through a process of juxtaposing in which findings on contexts and mechanisms will be used to explain outcomes observed. Subsequently, interpretation will be shared with the research team for scrutiny, discussion and verification.

### Phase 3: Refinement of IPT – 6 months

A few potential CMO configurations will be proposed. Stakeholder participants of phase 2 will be invited back for focus group discussions (FGD) to validate and ensure program evolution has been accounted for. The IPTs will be refined to highlight how to improve ViP by detailing what works (outcome), as well as how (mechanisms) and under what conditions (contexts).

